### Data Collection

#### Overview

Data will be collected using a mixed methods approach at the beginning, during, and at the end of the intervention. Data will be collected through questionnaires, document analyses, semistructured interviews, and structured observations and will cover different aspects of process evaluation.

The personal data collected are subject to the obligation of confidentiality and the provisions of data protection law. The data will be used exclusively for the purpose specified in the consent form. Initially, the data will be pseudonymized, and then they will be anonymized during the later course of the study. After completion of the study, the transcribed audio files will be deleted.

If available, the pseudonyms assigned in the main trial will be used. Patients will be referred for the process evaluation through the established central coordination and contact platform. The key list remains at the LMU. By agreeing to participate in an interview as part of the process evaluation, the patients explicitly consent to being contacted by the staff of the MLU.

All data collected are processed on access-protected computers and then stored safely and securely for 10 years at the Institute of Health and Nursing Science at the MLU. The pseudonymized data will not be passed on to third parties. The publication of the data takes place exclusively in an anonymized form.

All participants will receive information about the study, and informed consent will be obtained (Multimedia Appendix 2). Informed consent will be obtained by a member of the MLU evaluation team, except for patients whose consent will be obtained through the central coordination and contact platform. Interested persons will receive written information about the study project, with the opportunity to ask questions via a conversation. They will then be provided with a consent form to sign. Before data collection begins, there will be another opportunity to ask questions and confirm consent.

After the inclusion of the physicians from the hematologic and oncologic practices, the baseline characteristics are recorded using the web-based survey application LimeSurvey. The link to the survey and an individual access code will be sent to the practices via email. If necessary, an email reminder will also be sent.

Several interviews will be conducted in person, through video conference via Cisco Webex [20], or through telephone. Interview guides were developed for each target group and topic of interest, which will be piloted in the first 3 to 5 interviews and adapted, if necessary. The audio-recorded interviews will be transcribed. There is no plan to send the interview transcripts to the participants. Structured observations will be conducted using a protocol with guiding themes. The protocols will also be piloted during the first structured observations. The objectives of the data collection are described in subsequent sections and summarized in Tables 1 to 3.

**Table 1 table1:** Data collection on the context of the intervention.

Intervention components and participants			Method		Assessments
**Central platform for coordination and contact**					
	Physicians from the coordination platform and office-based hematologists and oncologists	Semistructured interviews		Experiences and facilitating and hindering factors regarding the contact platform	
**Onco Coach**					
	Onco Coach	Semistructured interviews		Baseline data (eg, vocational education and training and professional experience) and understanding of one’s role and expectations	
	Patients, hospital physicians, office-based hematologists and oncologists, and project participants of other intervention components	Semistructured interviews		Experiences and facilitating and hindering factors regarding cooperation	
**Digital project-specific case file**					
	Users (hospital physicians, office-based hematologists and oncologists, and project participants of other intervention components)	Semistructured interviews		Experiences and facilitating and hindering factors regarding the use of the case file	
	Office-based hematologists and oncologists	Questionnaire		Baseline data on the practice and person (location, area covered, connections to clinics or centers, composition and characteristics of the practice team, and IT equipment)	
**Patient app**					
	Patients and users of other intervention components (Onco Coach and psycho-oncologists)	Semistructured interviews		Experiences and facilitating and hindering factors regarding the use of the app	
**Virtual tumor board**					
	Hospital physicians and office-based hematologists and oncologists	Semistructured interviews and structured observation		Existing structures, experiences, and facilitating and hindering factors with regard to participation in and cooperation on the tumor board	
**Decision support tool**					
	Patients, office-based hematologists and oncologists, and hospital physicians	Semistructured interviews		Experiences and facilitating and hindering factors regarding the application	
**Decision coaching**					
	Patients and Onco Coach	Semistructured interviews		Experiences and facilitating and hindering factors regarding the decision coaching	
**Digital psycho-oncological offers**					
	Patients and psycho-oncologists	Semistructured interviews		Existing structures, experiences, and facilitating and hindering factors regarding the services offered	
**Training program**					
	Hospital physicians, office-based hematologists and oncologists, and Onco Coach	Semistructured interviews		Experiences and facilitating and hindering factors regarding the training program	

**Table 2 table2:** Data collection on the implementation process.

Intervention components and participants			Method		Assessments
**Central platform for coordination and contact**					
	Documentation of the central platform for coordination and contact	Document analysis		Number of contacts (medium and topic) and recruitment rate	
	Hospital physicians, Onco Coach, office-based hematologists and oncologists, and physicians from the contact platform	Semistructured interviews		Experiences regarding accessibility, cooperation, and consequences of the contact and changes during the process	
**Onco Coach**					
	Onco coach documentation	Document analysis		Number of contacts with patients, hospital physicians, and office-based hematologists and oncologists and medium and topic of the contact	
	Patients, Onco Coach, and hospital physicians	Semistructured interviews		Experiences regarding accessibility, cooperation, and consequences of the contact and changes during the process	
**Digital project-specific case file**					
	Users	Semistructured interviews		Application of the digital case file and exchange among participants with the help of the case file	
	IT department	Document analysis and semistructured interviews		Support requests and solutions and changes during the process	
**Patient app**					
	Patients and users of other intervention components (Onco Coach and psycho-oncologists)	Semistructured interviews		Use of the app and changes during the process	
	IT department	Document analysis and semistructured interviews		Support requests and solutions and changes during the process	
**Virtual tumor board**					
	Hospital physicians and office-based hematologists and oncologists	Semistructured interviews and structured observation		Tumor board procedure and cooperation between hospital physicians and office-based physicians and participation of office-based hematologists and oncologists	
**Decision support tool**					
	Patients, office-based hematologists and oncologists, and hospital physicians	Semistructured interviews		Use of the decision support tool	
	Decision support tool	Document analysis		Number of times the decision support tool was used and frequency of the topics for which the tool was used	
**Decision coaching**					
	Patients and Onco Coach	Semistructured interviews		Services offered and procedure of the decision coaching	
	Decision coaching documentation	Document analysis		Number of times decision coaching was carried out	
**Digital psycho-oncological offers**					
	Patients and psycho-oncologists	Semistructured interviews		Experiences and facilitating and hindering factors regarding the services offered	
	Documentation of the digital psycho-oncological offers	Document analysis		Cooperation with external psycho-oncologists	
**Training program**					
	Hospital physicians, office-based hematologists and oncologists, and Onco Coach	Semistructured interviews		Satisfaction and practical applicability of the contents	
	Training program documentation	Document analysis		Number of users and evaluation of test results	

**Table 3 table3:** Data collection on the mechanisms of impact.

Intervention components and participants			Method		Assessments
**Central platform for coordination and contact**					
	Physicians from the coordination platform and office-based hematologists and oncologists	Semistructured interviews		Experiences and attitudes regarding the contact platform in terms of care coordination	
**Onco Coach**					
	Patients, hospital physicians, office-based hematologists and oncologists, and project participants of other intervention components	Semistructured interviews		Experiences and attitudes regarding the services supplied by the Onco Coach in terms of care coordination	
**Digital project-specific case file**					
	Users (hospital physicians, office-based hematologists and oncologists, and project participants of other intervention components)	Semistructured interviews		Experiences and attitudes regarding the case file in terms of care	
**Patient app**					
	Patients and users of other intervention components (Onco Coach and psycho-oncologists)	Semistructured interviews		Experiences and attitudes regarding the app in terms of care	
**Virtual tumor board**					
	Hospital physicians and office-based hematologists and oncologists	Semistructured interviews		Experiences and attitudes regarding the tumor board in terms of care	
**Decision support tool**					
	Patients, office-based hematologists and oncologists, and hospital physicians	Semistructured interviews		Experiences and attitudes regarding the decision guide in terms of care	
**Decision coaching**					
	Patients and Onco Coach	Semistructured interviews		Experiences and attitudes regarding the decision coaching in terms of care	
**Digital psycho-oncological offers**					
	Patients and psycho-oncologists	Semistructured interviews		Experiences and attitudes regarding the services offered in terms of care	
**Training program**					
	Hospital physicians, office-based hematologists and oncologists, and Onco Coach	Semistructured interviews		Experiences and attitudes regarding the contents in terms of care	

#### Context of the Intervention

To better understand the mechanisms of change and identify barriers and facilitating factors for implementation, contextual factors will be examined. For this purpose, we will conduct semistructured interviews with responsible persons of the CCC Munich at different points during the intervention phase to explore existing structures, changes in structures, attitudes, and mutual influences. In addition, we will conduct semistructured interviews with the responsible persons, staff, and stakeholders of the intervention components and collect descriptive data on the existing resources. To better understand and describe the context in which hematologic and oncologic practices are embedded, we will also conduct semistructured interviews during the intervention phase. Baseline characteristics such as the location of the practice, practice structures, connections or cooperation with a clinic or center, and IT equipment will be assessed.

#### Implementation Process

We will document the implementation process of the intervention, success and failure of recruitment, and participation rates. To answer the question of how the intervention components were implemented, we will conduct semistructured interviews with all persons involved in the intervention (patients, physicians in hematologic and oncologic practices, and staff of the CCC Munich). Furthermore, we will address the question of whether individual intervention components were implemented as intended. This includes the fidelity of the intervention, the degree of implementation, conscious and unconscious adjustments, and the extent to which the respective components reached the target group. For this purpose, we will conduct quantitative and qualitative document analyses on different issues (eg, the number of participants in the training courses, the frequency of psycho-oncological consultations, the completeness of documentation, the use of the DST, and IT support). We will also use structured observations for individual intervention components (eg, the tumor board).

#### Mechanisms of Impact

To understand the impact of the intervention components on care coordination, we will conduct semistructured interviews with patients in the intervention group, physicians in hematology and oncology practices, persons and staff responsible for the intervention components, and physicians in the LMU and TUM. The aim is to understand the complex causal pathways and mediators of the intervention. The theoretical concept of care coordination will be the basis for the exploration. In particular, the focus is on the domains of communication and information (including all processes, communication, and information within the attending practice) and needs-based navigation (need-assessment and needs-based navigation outside the caregiver’s institution, including all stakeholders in the health care process). Furthermore, spontaneously reported unintended effects of both the intervention components and the process evaluation itself will be collected. Significant influences will be discussed with the project team.

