**Objective:**

This process evaluation will contribute to answering questions about intervention fidelity and the implementation of transsectoral communication, identifying and describing the intended and nonintended effects of the intervention, and exploring the barriers to and facilitators of the implementation.

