### Objective

TARGET consists of a variety of components that aim at different target groups, are offered by different groups of professionals, and concern different aspects of patient care. Therefore, a comprehensive process evaluation following the Medical Research Council guidance for process evaluation of complex interventions [9] is planned (1) to analyze contextual factors and their interactions with the intervention components; (2) to describe the intervention, its causal assumptions, and the implementation process; and (3) to assess the mechanisms of change such as participant responses and mediators. The aims are to assess intervention fidelity and the implementation of transsectoral communication, identify and describe the intended and nonintended effects of the intervention, and explore the barriers to and facilitators of implementation [9].

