## Discussion

### Overview

The TARGET project is a complex intervention that is to be implemented in an equally complex health care context. Whether the implementation is successful and the intervention achieves its desired effect depends on various factors and their interactions, for example, the contextual factors in the outpatient and clinical settings, the behavior and attitudes of the different stakeholders involved, and the intervention components in relation to routine care. A comprehensive analysis of processes and an assessment of diverse perspectives have been planned alongside a logic model. The logic model will guide data collection and analyses and is intended to help clarify causal assumptions. The findings of the primary outcome *coordination of care* from the patient’s perspective, measured using the validated German version of the Care Coordination Instrument [8], will be accompanied by in-depth interviews with patients and perspectives of physicians. The results will finally be reported according to the Template for Intervention Description and Replication (TIDieR) checklist [23].

The summative evaluation study will follow a parallel group design, and eligible patients will be a heterogeneous group in terms of diagnosis, stage of disease, and course of treatment. Therefore, a comprehensive process evaluation is all the more important to understand the influence of contextual factors, assess the mechanisms of change, identify intended and nonintended effects, and explore the barriers to and facilitators of implementation.

As the evaluators who conduct the process evaluation are an external team from the MLU, it is important to establish a good working relationship with all the stakeholders involved in the intervention development and implementation to ensure a close observation of the intervention. Maintaining sufficient independence while observing the work of the different stakeholders is crucial. Another challenging question is whether the emerging findings should be communicated to the stakeholders. The evaluators can either act as passive observers reporting the results at the end of the project or help correct implementation problems while they occur [9]. We will not engage in continuous quality improvement activities because this might compromise the external validity of the evaluation [9], although serious observations will be discussed with the project team.

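### Nonintended effects are a stated aim, but the only collection route named for them is spontaneous reporting, so those not volunteered are likely to be under-detected

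*Protocol article*

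**What the plan says.** The aim appears three times in the protocol article. The abstract's Objective speaks of "identifying and describing the intended and nonintended effects of the intervention", the Objective in the Introduction repeats it as "identify and describe the intended and nonintended effects of the intervention", and the Discussion (Overview) gives it as a reason for a comprehensive process evaluation: to "identify intended and nonintended effects, and explore the barriers to and facilitators of implementation".

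The method appears once, in Data Collection, Mechanisms of Impact: "spontaneously reported unintended effects of both the intervention components and the process evaluation itself will be collected". The same paragraph frames the impact interviews differently: "The theoretical concept of care coordination will be the basis for the exploration".

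Tables 1 to 3 list the assessments for nine intervention components. A typical Table 3 entry is "Experiences and attitudes regarding the app in terms of care", and a typical Table 1 entry is "Experiences and facilitating and hindering factors regarding the use of the app". The Overview of Data Collection adds that "Interview guides were developed for each target group and topic of interest". The guides themselves are not reproduced. The Limitations section does not mention reliance on spontaneous reports.

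**The concern.** In its ordinary meaning, a spontaneous report is one given without being asked for. For a named aim, this is a passive method: what reaches the data depends on whether a participant thinks of an effect, links it to the intervention and chooses to raise it. Barriers, experiences and attitudes all appear as assessment topics in the tables. Nonintended effects do not.

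At stake is how far the evaluation can meet the aim. If few unintended effects are reported, a reader could not tell whether few occurred or few were volunteered. That matters here because the Conclusions say the process evaluation is meant to help interpret the results of the main trial and to inform projects that adapt the intervention or its parts.

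**Working it through.** **Step 1: aim against method.** The aim covers intended and nonintended effects together. The only sentence that names a collection route for the second group restricts it to spontaneous reports. No other sentence in Data Collection or Data Analysis assigns a method to unintended effects.

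**Step 2: do the tables supply another route?** All nine components were checked in each table.

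| Source | Closest assessment | Coverage | Does it target unintended effects? |
|---|---|---|---|
| Table 1, interviews | Hindering factors | All nine components | No. These are barriers to use or cooperation; some effects may emerge |
| Table 2, interviews | Consequences of the contact | Contact platform and Onco Coach | Partly. Unwanted consequences fit the wording, but for two of nine components |
| Table 2, document analysis | IT support requests and solutions | Case file and patient app | Partly. Technical problems only |
| Tables 1 and 2, observation | Tumor board structures, procedure and cooperation | Tumor board | Partly. What is visible during the board |
| Table 3, interviews | Experiences and attitudes, in relation to care coordination (two components) or care (seven) | All nine components | Not named. The wording is neutral in direction |

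There are therefore partial, indirect routes, but no assessment that asks about unintended effects as such.

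**Step 3: what unprompted reporting could cost, as an illustration only.** The document gives no detection figure, so there is nothing to reproduce. Let n be the number of interviews, p the share of interviewees who experience an effect and m the share of those who disclose it. The chance of at least one report is

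D = 1 − (1 − p·m)^n.

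Inputs: n = 40 patient interviews (approximate) and n = 10 to 15 hospital physician interviews, both from Participants and Recruitment. The values of p and m are assumptions. The case m = 100% is the ceiling for direct questioning.

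Patients, n = 40, p = 5%:
- m = 100%: 1 − 0.95^40 = 0.87
- m = 50%: 1 − 0.975^40 = 0.64
- m = 25%: 1 − 0.9875^40 = 0.40
- m = 10%: 1 − 0.995^40 = 0.18

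Patients, n = 40, p = 10%:
- m = 100%: 1 − 0.90^40 = 0.99
- m = 50%: 1 − 0.95^40 = 0.87
- m = 25%: 1 − 0.975^40 = 0.64
- m = 10%: 1 − 0.99^40 = 0.33

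Hospital physicians, p = 10%:
- m = 100%: 0.65 (n = 10) to 0.79 (n = 15)
- m between 10% and 50%: from 0.10 (n = 10, m = 10%) to 0.54 (n = 15, m = 50%)

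The direction follows whenever asking raises disclosure. The size is set entirely by the assumed p and m. The formula also treats interviewees as a random sample, whereas the protocol uses theoretical sampling and lets saturation decide the number.

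**The case against.** The strongest case on the other side has four parts.

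- **The text does not confine collection to spontaneous reports.** The sentence is introduced as an addition and contains no word of exclusion. This stands. A reader might infer that unintended effects are recorded only if volunteered, and so found only by chance, but the document does not say that, and the partial routes in Step 2 count against it. What remains is that spontaneous reporting is the only route named for these effects.
- **No tilt towards benefit is shown.** A reader might infer that intended effects are actively sought for every component while unwanted ones are not. The tables do not support this. The Table 3 wording is neutral, only two of the nine components refer to care coordination, and no row asks specifically for intended effects.
- **The interview guides are not shown.** They may contain an open prompt on unexpected effects, and an article commonly leaves such content to fuller documents. This limits what can be concluded about practice, but the point rests on a method that is stated, not on one that is absent. If the guides do ask, the stated method is inaccurate.
- **The illustration omits informants and other data.** It leaves out intervention staff and practice physicians, who are also interviewed. The main trial separately measures symptoms, quality of life and survival. Both are true. For the same reason, the claim that silence would be read as absence of harm goes too far: nowhere does the document say that it will draw that inference.

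**Conclusion.** The mismatch is real and moderate. An aim stated three times has one named collection method, that method is passive, and no table entry targets the aim. Unintended effects that participants do not volunteer, and that do not surface through hindering factors, consequences of contact, IT records or tumor board observation, are likely to be under-detected.

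The extent cannot be derived from the document. The probabilities above show only the direction and how strongly it depends on disclosure. The conclusion assumes that the word for spontaneous reporting carries its ordinary meaning, and that a direct question would prompt at least some people who would otherwise stay silent.

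**What to change.** 1. Amend the sentence under Mechanisms of Impact so that it covers unintended effects that are spontaneously reported and those that are actively elicited. Elicitation should supplement spontaneous reports, not replace them.
2. Add one neutral open question on unexpected or unwanted effects to each remaining interview guide, and one field to the structured observation protocol.
3. List unintended effects as an assessment in Table 3.
4. Code solicited and spontaneous reports separately, so that interviews with and without the question are not pooled unknowingly.
5. If the guides already include such a prompt, correct the sentence to say so; steps 2 to 4 then apply only where something is missing.

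The cost is slightly longer interviews and a notice to the ethics committee, which is to be told of procedural changes (Ethical Considerations). The protocol ties adaptation of the guides to piloting in the first 3 to 5 interviews, but Data Analysis describes collection as iterative and Limitations expects further questions to arise. Data collection began on March 14, 2023, with recruitment expected to run to September 30, 2025, so interviews held before the change would lack the question. That should be reported as a limitation. If no change is made, the aim should be narrowed to volunteered effects and the reliance on them acknowledged.
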